## Abstract

**Background:**

Irritable bowel syndrome (IBS) is one of the most common functional gastrointestinal disorders characterized by recurrent abdominal pain associated with defecation or a change in bowel habits. Leading to significant negative effect on patients’ quality of life and huge financial burden to health system, the management of IBS is a great challenge. Probiotics are considered as an effective therapy; however, in a lack of high-quality evidence of efficacy, no strain- and dose-specific probiotics were recommended in clinical guidelines. This study aims to evaluate the efficacy of the *Bifidobacterium* quadruple viable tablet in the treatment of IBS-D.

**Methods/design:**

A multicenter randomized controlled trial will be performed in fourteen hospitals. A total of three hundred patients who fulfill the eligibility criteria will be stratified divided into an experimental group and a control group randomly in a ratio of 1:1. The experimental group is treated with the *Bifidobacterium* quadruple viable tablet while the control group is treated with placebo. All the patients will receive a 4-week treatment and a 2-week follow-up. The primary outcome is the effectiveness in improving abdominal pain and stool consistency; the secondary outcome includes evaluation of overall symptom relief, frequency of defecation, bloating, urgency of defecation, remedial medication, score of IBS-QOL, and changes of microbiota and metabonomics. Physical examination, vital signs, laboratory tests, adverse events, and concomitant medication will be taken into account for intervention safety assessment during the trial.

**Discussion:**

This multicenter randomized controlled trial may provide high-quality evidence on the efficacy of the *Bifidobacterium* quadruple viable tablet for IBS-D on both physical and mental dimensions in China. To fill the gap of previous probiotic intervention studies, in addition, this study will also present safety assessment which will be a significant emphasis.

**Trial registration:**

ChiCTR1800017721. Registered on 10 August 2018.

## Administrative information

Note: the numbers in curly brackets in this protocol refer to SPIRIT checklist item numbers. The order of the items has been modified to group similar items (see http://www.equator-network.org/reporting-guidelines/spirit-2013-statement-defining-standard-protocol-items-for-clinical-trials/).

## Introduction

### Background and rationale {6a}

Irritable bowel syndrome (IBS) is one of the most common functional gastrointestinal disorders characterized by recurrent abdominal pain associated with defecation or a change in bowel habits [1, 2]. The prevalence is estimated between 5 and 20% worldwide [3]. Based on the predominant disorder in bowel habits, IBS is classified into four subtypes: constipation predominant IBS (IBS-C), diarrhea predominant IBS (IBS-D), IBS with mixed bowel habits (IBS-M), and unclassified IBS (IBS-U). Among them, IBS-D is the most common one with a proportion of nearly 60% in IBS according to a cross-sectional survey [4]. Although IBS-D affects patients’ quality of life and brings huge financial burden to health system, the management is still a great challenge [5, 6].

Nowadays, more and more studies focus on the role of microbiota in patients with IBS [7–12]. Recently published studies found that compared with normal participants, there is a significant reduction in beneficial bacteria such as *Bifidobacteria* and *Lactobacilli*. Instead, an increase of *Escherichia coli* in patients with IBS-D is observed [11, 12]. Therefore, the change of the microbiota is deemed as an important etiology of IBS-D.

A newly published systematic review supported the benefits of probiotics for patient with IBS, but there was significant heterogeneity as for the various kinds and dose of probiotics [13]. Besides, there are very few high-quality randomized controlled trials with rigorous design [13, 14]. As a result, we need further strong evidence to guide us as for the clinical choice of probiotics.

The *Bifidobacterium* quadruple viable tablet is a new candidate of probiotic product developed and produced by Hangzhou Grand Biologic Pharmaceutical. INC (patent number: ZL01108353.0; International Patent Classification: A61K 35/74). The *Bifidobacterium* quadruple viable tablet is a compound microecological preparation consisting of *Bifidobacterium infantis*, *Lactobacillus acidophilus*, *Enterococcus faecalis*, and *Bacillus cereus*, combining anaerobic with aerobic bacteria. On the one hand, *Bifidobacterium infantis*, *Lactobacillus acidophilus*, and *Enterococcus faecalis* are normal intestinal microbiota inside the intestinal tract of healthy human body. Studies found that direct supplementation of microbiota above can inhibit certain pathogenic bacteria and leads to normal intestinal peristalsis and balance of intestinal microbiome [15–20]. On the other hand, *Bacillus cereus* can colonize in the intestinal tract. They consume oxygen and create an anaerobic environment for anaerobic bacteria to promote the growth and reproduction of anaerobic bacteria such as *Bifidobacteria* [21]. We speculated that the four strains of the *Bifidobacterium* quadruple viable tablet can collaborate to multitarget improvement of the intestinal microenvironment, which indicated a potential therapeutic effect on IBS-D.

### Objectives {7}

The aim of this trial is to evaluate the efficacy of the *Bifidobacterium* quadruple viable tablet in the treatment of IBS-D.

### Trial design {8}

This study is a parallel, double-blind, placebo-controlled, multicenter randomized controlled trial (RCT). The trial will include three periods: a 2-week screening period, a 4-week treatment period, and a 2-week follow-up period. During the screening period, patients will record a symptom diary every day including abdominal pain intensity, stool consistency, evaluation of symptom remission, and the changes in the pattern of bowel movement. Those who record all items in the symptom diary for at least 10 days during the screening period and fulfill the eligibility criteria will be randomized at a ratio of 1:1 into either the *Bifidobacterium* quadruple viable tablet group or the placebo group. The time schedule and outcome assessment of the trial are presented in Figs. 1 and 2.

**Fig. 1 Fig1:**
[figure not shown]
Flowchart of study

**Fig. 2 Fig2:**
[figure not shown]
Study schematic diagram. IBS, irritable bowel syndrome; HAMA, Hamilton Anxiety Scale; HAMD, Hamilton Depression Scale; IBS-QOL, IBS-Quality of Life Questionnaire; ECG, electrocardiogram

The protocol design is based on the Standard Protocol Items: Recommendations for Interventional Trials (SPIRIT) 2013 Checklist (Additional file 1). The overall supervision of our trial will be under the charge of the Clinical Trial Ethics Committee of Huazhong University of Science and Technology; any changes in the protocol will be submitted to and decided by the Ethics Committee. Subjects will receive timely medical treatment when adverse reactions occur during the trial; participants’ health and safety will be the top priority. There will be sufficient time leaving for patients to consider whether to participate in the trial or not.

## Methods: participants, interventions and outcomes

### Study setting {9}

A total of 300 patients diagnosed with IBS-D will be divided randomly into 2 groups (the *Bifidobacterium* quadruple viable tablet group and the placebo group) in a ratio of 1:1. The study is being conducted in the following fourteen hospitals: Wuhan Union Hospital, Peking Union Hospital, Chinese Academy of TCM Wangjing Hospital, Beijing Jishuitan Hospital, The Affiliated Sir Run Run Shaw Hospital of Zhejiang University School of Medicine, Zhejiang Provincial Hospital, Jilin University China-Japan Friendship Hospital, Jilin Provincial People’s Hospital, The First People’s Hospital Of Luoyang, The First People’s Hospital Of Xinxiang, Lianyungang City Hospital, Jingzhou Chinese Hospital, Yan’an University Affiliated Hospital, and The Second Affiliated Hospital of Shandong University of Chinese Medicine.

### Eligibility criteria {10}

#### Inclusion criteria

Patients participated voluntarily and signed informed consent.Aged 18–65 years old.Patients were diagnosed as diarrhea predominant irritable bowel syndrome (IBS-D) by Drossman 2016 [22].After 2 weeks of screening (7 days before the beginning of treatment), patients have abdominal pain at least 2 days a week, and the mean value of the most severe abdominal pain was more than 3 (11—NRS report). Meanwhile, the fecal traits were classified as type 6 or 7 at least 2 days.During the screening period (14 ± 3 days before the onset of treatment), the patients completed the symptom diary for at least 10 days.Patients discontinued the drugs used in the pre-screening stage for abdominal symptoms or diarrhea.The lifestyle during the visit (from the first visit before screening to the last visit of the trial) did not make any significant changes in the symptoms of diarrhea and abdominal pain (for example, starting a new diet, or changing the usual exercise pattern).Colonoscopy report within 2 years of tertiary hospitals in China was normal, or the researchers considered no clinical significance (such as chronic colitis diagnosed by congestion and edema, but no erosive ulcer; the diameter of colonic polyps was less than 3 mm, and the number was less than 5).

#### Exclusion criteria

Having intestinal organic diseases, such as inflammatory bowel disease, intestinal tuberculosis, malabsorption syndrome, celiac disease, lactose intolerance, or other organic diseases.Having history of abdominal and pelvic surgery, such as cholecystectomy (patients who accepted appendectomy; patients who did not have intestinal complications after cesarean section, such as intestinal obstruction; and patients who accepted endoscopic treatment of intestinal polyps can be included).Having chronic pancreatitis, tumors, peptic ulcers, tuberculous peritonitis, chronic liver disease, liver cirrhosis, and other digestive system non-intestinal diseases (B ultrasonic diagnosis of chronic cholecystitis patients without typical biliary colic can be included).Stool routine results were abnormal: fecal occult blood (+) or red blood cells (+) or white blood cells (+).Having other serious systemic diseases, including serious diseases such as heart, lung, kidney, and other important organ diseases; immunomodulatory diseases; metabolic diseases (diabetes, hyperthyroidism, or hypothyroidism) or malignant tumors; and other diseases such as ovarian cysts and endometriosis.Laboratory tests showed significant abnormalities: (1) hemoglobin < 1 × LLN; (2) serum creatinine was more than 1 × ULN, or creatinine clearance was less than 1 × LLN; (3) abnormal liver function is defined as AST > 1.5 × ULN and/or ALT > 1.5 × ULN and/or total bilirubin > 1.5 × ULN.Patients with severe mental illness or HAMD score > 20 points, or HAMA score > 29 points.Abdominal pain occurs mainly at night during the screening period; patients with unexplained emaciation, fever, jaundice, bloody stool, or black stool; or BMI < 17.Patients with a history of drug abuse or alcohol abuse (the abnormal adaptation caused by alcohol or drug use can lead to clinical morbid state, and at least 1 manifestations in 12 months: ① repeated use of drugs or alcohol to cause negligence or failure in work, academic, or family responsibility, and ② use drugs or alcohol repeatedly on occasions where the body is in danger; ③ legal problems related to the use of drugs or alcohol repeatedly; and ④ although drugs or alcohol causes social or interpersonal problems, they continue to use this substance) and those who are allergic to the drug.During the experiment, the accompanying drugs that affect gastrointestinal motility and function cannot be stopped, such as antibiotics, intestinal microecologic agents, and proton pump inhibitors.Pregnant or breastfeeding women who plan to be pregnant during the trial period.Less than 3 months after attending or completing other clinical trials.Researchers think it is not suitable for the candidates.

### Who will take informed consent? {26a}

Informed consent will be acquired before screening test. All patients recruited will be informed of all contents involved in this trial in oral and written form both by their responsible investigators. There will be sufficient time for patients to consider whether to participate and raise any questions at their concern. And patients who are willing to participate will be required to sign informed consent paper.

### Additional consent provisions for collection and use of participant data and biological specimens {26b}

The investigators must obtain written informed consent for the participation in blood and stool sample collection from each participant before the trial.

### Interventions

#### Explanation for the choice of comparators {6b}

Each *Bifidobacterium* quadruple viable tablet contains a minimum of 0.5 × 106 cfu *Bifidobacterium infantis*, *Lactobacillus acidophilus*, and *Enterococcus faecalis* plus a minimum of 0.5 × 105 cfu *Bacillus cereus*. The placebo tablet contains corn starch without probiotics. The *Bifidobacterium* quadruple viable tablets and the placebo tablets are identical in color, appearance, and packaging. Both of them will be produced and provided by the Hangzhou Grand Biologic Pharmaceutical. INC. (Hangzhou, Zhejiang Province, China).

#### Intervention description {11a}

Subjects of two groups will receive three tablets of either the *Bifidobacterium* quadruple viable tablet or the matched placebo three times a day at 30 min after breakfast, lunch, and dinner, respectively, for consecutive 4 weeks. During the treatment period, researchers will give subjects physical exams and record the results as well as vital signs. Subjects are supposed to keep completing the symptom log every day and record remedial medication and any other drug history permitted in this trial. HAMA, HAMD, IBS-QOL, and laboratory tests will be updated at the end of treatment period.

### Criteria for discontinuing or modifying allocated interventions {11b}

#### Withdrawal criteria

##### Determined by investigator

In cases of worsening disease or concomitant complications with a necessity of safety evaluation and curative treatment.With forbidden therapy and medication history during the trial which will lead to bias for efficacy and safety evaluation.

##### Participant request

Patients will be allowed requesting to quit due to their priority, and then, their treatment will abort, regarded as shedding cases and recorded as “treatment failure.” Reasons for withdrawal will be followed and recorded in symptom diary while CRF of every patients will be saved for data analysis,

When subjects with relief of symptoms are unwilling to continue taking the treatment, they need to stop the medication with the researchers’ consent. And the 4-week follow-up will still be conducted after medication as planned.

### Strategies to improve adherence to interventions {11c}

During the trial, experimental drugs and symptom diary will be delivered to patients in the ex-period and returned after the period to ensure the process will be conducted as good as expected. Investigator shall inform patients at the beginning of the trial repeatedly to ensure that they fully understand the importance of timely medication. Patients will be requested to record the code of drugs, date, dose, and time when taking medication in the diary. The diary, leftover medicine, and package will be recycled after the follow-up period, and the tablets will be counted to comprehensively evaluate patients’ compliance to the treatment.

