### Methods for additional analyses (e.g., subgroup analyses) {20b}

The full analysis set (FAS), the per protocol set (PPS), and the safety set (SS) will be included for analysis. The FAS will be obtained on the basis of intention-to-treat (ITT) population, after exclusion from all randomized subjects who receive at least a single-dose treatment through a minimum and rational method. Last-observation-carried-forward will be applied for the estimation of missing data. The PPS is defined as a set including all patients meeting the eligibility criteria; finishing the treatment without major protocol deviations, with good compliance (between 80 and 120%); and completing the CRF as anticipated. The safety set will include those who receive at least a single-dose treatment with data of safety evaluation. Carry-forward of missing data will not be in demand.

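### The adherence section gives two different times for the return of study drug and diary; the later one, after follow-up, weakens the tablet count and the week 5–6 data

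*Protocol article*

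**What the plan says.** The section Strategies to improve adherence to interventions {11c} has three relevant sentences.

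- It opens with "experimental drugs and symptom diary will be delivered to patients in the ex-period and returned after the period". Which period is meant is not stated.
- It then sets up a dated intake record: "Patients will be requested to record the code of drugs, date, dose, and time when taking medication in the diary".
- It closes by saying that the diary, "leftover medicine, and package will be recycled after the follow-up period, and the tablets will be counted", in order to evaluate compliance.

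Trial design {8} has "a 2-week screening period, a 4-week treatment period, and a 2-week follow-up period". Participant timeline {13} puts treatment at day 1 to 28 ± 3 and follow-up at day 29 to 42 ± 3. Dosing is three tablets "three times a day at 30 min after breakfast, lunch, and dinner, respectively, for consecutive 4 weeks" (Intervention description {11a}).

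Methods for additional analyses {20b} limits the per-protocol set (PPS) to patients "finishing the treatment without major protocol deviations, with good compliance (between 80 and 120" per cent). It gives no formula for compliance.

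Under Participant request in {11b}, patients whose symptoms are relieved may stop the tablets with the researchers' consent and remain in follow-up. That section calls the follow-up 4 weeks long, whereas Trial design has 2 weeks; these two statements also need to be reconciled.

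**The concern.** The opening and closing sentences of {11c} can send sites in different directions. One can be read as return at the end of each period. The other puts collection and counting of leftovers after a follow-up in which no dosing is planned.

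Under the closing sentence, a patient with leftover tablets keeps them for two more weeks. Two things are then at stake:

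- **Compliance.** A count at about day 42 measures every tablet that has left the package by then, whether taken in weeks 1–4, taken in weeks 5–6, or lost. A patient below 80% during treatment could appear to be above it and enter the PPS.
- **Follow-up data.** The week-6 IBS-QOL, the follow-up HAMA and HAMD, and the week 5–6 diary are meant to describe patients after treatment. Use of leftovers would mix time on and off treatment.

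The closing sentence also covers the diary. Read literally, the weeks 1–4 booklet, which supplies both components of the primary outcome, would stay with the patient until follow-up ends.

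**Working it through.** **The plan's own figures.** The 80–120% window is a rule without a derivation, so there is nothing to reproduce. The sample size is not in dispute and reproduces. For 50% against 30%, two-sided α = 0.05 and 90% power, with pooled variance under the null:

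n = [1.960·√(2·0.4·0.6) + 1.282·√(0.25 + 0.21)]² / 0.20² = 124 per arm, as stated.

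**Inputs.** 3 tablets × 3 times a day = 9 a day, for 28 days {11a}. Follow-up is 14 days {8, 13}. The limits are 80% and 120% {20b}. The number of tablets dispensed is not stated; I assume exactly 252 unless noted.

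**Step 1: expected tablets and limits.**
- Expected: 9 × 28 = 252 (225 for 25 days, 279 for 31 days, given the ± 3-day window).
- 80% limit: 0.8 × 252 = 201.6, so 202 tablets.
- 120% limit: 1.2 × 252 = 302.4 tablets.

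**Step 2: effect of one late day.** If compliance were computed from the count as (dispensed − returned) / 252, each full-dose day in weeks 5–6 would add 9 / 252 = 3.6 percentage points.

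**Step 3: late tablets needed to reach 202.**

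| Compliance in weeks 1–4 | Tablets taken | Late tablets to reach 80% | Days at 9 a day |
|---|---|---|---|
| 79% | 199 | 3 | 0.3 |
| 75% | 189 | 13 | 1.4 |
| 70% | 176 | 26 | 2.9 |
| 60% | 151 | 51 | 5.7 |
| 50% | 126 | 76 | 8.4 |

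All of these fit inside 14 days.

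**Step 4: worst case for follow-up.** The 70% complier holds 252 − 176 = 76 tablets, and 76 / 9 = 8.4 days, or 8.4 / 14 = 60% of follow-up. Using all of them makes a day-42 count read 252 / 252 = 100%. If the supply covered 31 days (an assumption), the same patient would hold 279 − 176 = 103 tablets, or 11.4 days, and a fully adherent patient ending on day 28 would hold 27, or 3 days.

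**Step 5: early stoppers.** A patient who stops at day 14 holds 252 − 126 = 126 tablets. Because the PPS also requires finishing the treatment, these patients bear mainly on the follow-up data.

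**Step 6: upper limit.** No one can exceed 120% on a supply of 252. That would need more than 302 tablets dispensed.

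**The case against.** The strongest reply is that the opening sentence of {11c} already has drug and diary come back at the end of each period, so that the closing sentence only describes final accountability. That reading is possible. A reader might infer from the closing sentence that patients certainly keep their tablets until week 6; the section does not settle this. What stands is that the two sentences are not reconciled.

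Second, the intake diary records date, dose and time, so late use that is honestly recorded can be seen. This is a real safeguard. It is nevertheless self-report, which the tablet count is there to check, and it does not ask about lost or discarded tablets.

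Third, a reader might infer that the tablet count defines the 80–120% rule. The protocol does not say so: {20b} gives only a range, and {11c} treats the count as part of a comprehensive evaluation. A move from 70% to 100% therefore assumes a count-only rule.

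Fourth, dosing is limited to 4 consecutive weeks, so late dosing would be a deviation that the return schedule makes possible, not one that it permits. Nothing indicates how often it would happen, and under double blinding nothing suggests that it would differ by arm. Tablets can also be discarded before day 28; earlier collection shortens that exposure without removing it.

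Fifth, Data management {19} has investigators collect information at each follow-up and enter it in the electronic system. The text therefore does not show that primary-outcome data wait until week 6. This part of the concern is weak, though the return time of the diary still needs to be clear.

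**Conclusion.** The point holds as an internal conflict over when study drug and diary are returned and counted, with a limited but real consequence if sites follow the later instruction. On a supply of exactly 252 tablets, and with the count used for compliance, a 70% complier crosses the 80% limit with 26 late tablets (2.9 days); at most 8.4 of the 14 follow-up days would be on treatment. These are worst-case figures that require a protocol deviation of unknown frequency.

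The reach is PPS membership and the week 5–6 data: IBS-QOL, HAMA and HAMD, and the diary. A reader might go further and conclude that the primary result is compromised. The documents do not support that: the primary outcome is assessed over the 4 treatment weeks, so tablets taken afterwards touch neither the primary analysis in the full analysis set nor the sample size. The protocol also states no hypothesis about persistence of effect after treatment. The correction is still worth making, because the rule as written weakens its own compliance check and the remedy is almost free.

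**What to change.** Reconcile the two sentences of {11c} along these lines:

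- Leftover tablets, packages and the treatment-period diary are returned, and the tablets counted, at the end-of-treatment assessment (day 28 ± 3).
- A separate diary is issued for follow-up.
- The tablet-count part of compliance uses that count, with 9 × the patient's actual number of treatment days as the denominator. The dated intake diary remains the second source.

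No new visit is needed: HAMA, HAMD, IBS-QOL and laboratory tests are already updated at the end of treatment {11a}, and stool is collected at week 4. The cost is an edit to one section and a second diary booklet. The change makes the count reflect the treatment period only and removes leftover study drug from follow-up.
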